**Fig 1 pone.0285858.g001:**
[figure not shown]
Effects of the POWER Up implementation strategies on the PrEP care continuum.

We hypothesize the following effects: 1) women at the CHCs will demonstrate a clinically meaningful increase in PrEP uptake and persistence at 3 and 6-months post-baseline, with 10% of PrEP-eligible Black women initiating PrEP and 30% of women who initiate PrEP persisting, and 2) the implementation of these strategies will be fully adopted by ≥80% of clinic partners and will achieve ≥ 90% ratings of satisfaction and acceptability by clinical partners and patients, and PrEP eligibility assessment will reach ≥ 50% of Black women.

## Materials and methods

### Aims and objectives

The aim of this study is to assess the acceptability and feasibility of implementing POWER Up as part of routine care in CHC settings and to assess the adaptation and efficacy of the implementation strategy package as it is implemented by comparing pre- and post-implementation rates of PrEP prescription among Black women at each CHC. The project has three specific aims. Aim 1 is to undertake qualitative data collection through provider and patient focus group discussions (FGDs) to inform the adaptation and implementation of POWER Up strategies for engaging Black women in the PrEP care continuum for use in CHCs. Aim 2 is to measure the implementation and effectiveness outcomes of the adapted bundle of implementation strategies in the Southern United States compared to the approach in the Midwest. This aim will be accomplished via a stepped-wedge cluster randomized trial (SW-CRT) to measure change in implementation outcomes and evaluation using the Reach, Effectiveness, Adoption, Implementation, and Maintenance (RE-AIM) framework. We will implement the POWER Up strategies across diverse geographic areas and assess the change in clinical and implementation outcomes from the pre-implementation (control) and the post-implementation (implementation) periods. The cluster, or unit of analysis, is each CHC, N = 12 (8 in the South, 4 in the Midwest). Aim 3 is to develop an implementation guide that can be utilized across U.S. jurisdictions to improve PrEP care continuum engagement among Black women, reflecting the knowledge gained through the adaptation and evaluation processes.

### Settings

POWER Up is being rolled out sequentially in 12 CHCs among 3 health networks in the Southern and Midwestern United States: Advance Community Health (North Carolina), Evara Heath (Pinellas County, Florida) and Erie Family Health Centers (Cook County, Illinois). Two of the health networks are located within priority jurisdictions of the CDC’s Ending the HIV Epidemic (EHE) initiative based on the high burden of HIV infection (Pinellas County, FL and Cook County, IL) [34]. These networks were selected due to their area’s elevated incidence of HIV, as well as the high volume of PrEP-eligible Black women who receive care at their sites. POWER Up has not been replicated elsewhere, so it is important to consider geographic location as a factor in implementation success. Although the goal of this project is to improve PrEP care continuum outcomes among Black women in the South, we are also including Midwestern sites to serve as a comparison in effectiveness to Southern sites. We chose to include different geographic regions so that the dissemination guide is relevant nationally to increase the likelihood that POWER Up strategies are able to be implemented nationwide. All participating CHCs currently have very low PrEP usage among Black women (less than 1%) who receive care at their sites, and none of the CHC sites have previously implemented the bundle of POWER Up strategies.

### Study design

We will utilize a SW-CRT to measure change in our primary implementation outcome, PrEP uptake. This study design will allow us to roll out the bundle of implementation strategies across diverse geographic areas and to assess the change in clinical and implementation outcomes from the pre-implementation (control) and the post-implementation (implementation) periods. There will be 12 clusters: 8 CHCs in the South and 4 CHCs in the Midwest (N = 12). In a stepped-wedge study, each clinic contributes both time and observations to the control condition (usual care) and the implementation condition (implementation of POWER Up strategies). Every clinic switches from the control to the implementation at regular time intervals (steps), but at different points in calendar time depending on randomization order [35]. Additionally, more than one clinic may start the bundle of POWER Up implementation strategies at a step. The design uses repeated cross-sectional collection of data, with our primary outcome obtained from patients seen during each time period (each step) at each clinic rather than following individually recruited patients over time. For our two PrEP persistence measures, patients are followed longitudinally after starting PrEP. This is a robust design because each clinic provides data under both the control and implementation conditions, reducing variability between the two conditions and improving precision when intra-cluster correlation is high, which is likely among the CHCs that we have chosen. As stepped-wedge designs consist of a unidirectional move from control to implementation, the bundle of POWER Up strategies is not withdrawn once implemented, alleviating ethical concerns [36].

In our stepped-wedge design, each step is 6 months long, and there are 4 waves of implementation (Fig 2). Three CHC sites will be randomized to each step, with a mix of sites from the South and the Midwest included. Each cluster also undergoes a 6-month transition period when the individual clinics will prepare to implement the bundle of POWER Up strategies. The sequence of switching from control to implementation condition at each site (each cluster) will be determined using a computer-based list randomization application to create 4 waves of implementation (three sites begin the implementation at the same step, a mix from the South and the Midwest).

**Fig 2 pone.0285858.g002:**
[figure not shown]
Timeline of stepped-wedge cluster randomized trial (SW-CRT) design (control, transition, and implementation periods).

### Study procedures

#### Data collection: Pre-implementation phase

The pre-implementation phase will occur from September 2021 to June 2023. During this phase, we will engage our expert advisory board–a group of medical providers, public health scientists specializing in PrEP implementation research, and Black women who have experience with HIV/PrEP. We will identify and engage with clinical champions at each health network to assist in the implementation design and provide feedback on local implementation. We will also conduct focus groups with providers and Black women patients at each of the clinic sites. Providers will be recruited using convenience sampling via email invitations at each clinic. Providers will respond to the email if interested in study participation. Flyers with the study team’s contact information will also be distributed to providers. Providers will be eligible to participate if they are 1) aged 18 years or older, 2) currently employed at one of the participating health network sites, 3) able to speak and understand English, and 4) provide informed verbal consent. Patients will be recruited at each CHC through flyers and routine phone calls made by staff, who will inform patients about the study. CHC staff will provide interested patients with the study team’s contact information, and patients will initiate contact with the study team. We will also provide a QR code on the flyer that will take patients to a study information page and eligibility screening form hosted on the University of Chicago’s secure web-based application, Research Electronic Data Capture (REDCap). The landing page will provide information about the focus groups, and patients will be able to enter their name and contact information so that the study team can screen patients for eligibility and contact them if eligible. To supplement passive recruitment by CHC staff, the study team will actively recruit in-person as needed at the study sites and conduct in-person eligibility screenings and focus groups. Patients will be eligible to participate if they 1) are aged 18 years or older, 2) are a current patient at one of the participating health network sites, 3) are able to speak and understand English, 4) identify as a Black/African American cisgender woman, and 5) provide informed verbal consent. Providers will be asked about PrEP training/education, existing PrEP education (e.g., brochures, flyers) available at their clinic, contextual factors that may inform adaptation of implementation materials, and workflow/approach to patient care (e.g., on-site pharmacy, blood draws available on site). The patient FGD guide will assess patients’ knowledge of and experience with PrEP, thoughts on PrEP education and being offered PrEP, suggestions for PrEP navigation services, and contextual factors influencing clinic environment and decision making about PrEP. After conducting focus groups and analyzing the qualitative data, we will use our findings to create relevant adaptations for each site (i.e., tailored provider training curricula and patient education materials/visuals).

#### Data collection: Implementation phase

In preparation for the implementation phase, we created a table of desired EMR variables that will be collected from each CHC throughout the implementation period (Table 1). These variables will be collected from July 1, 2023 to December 31, 2025. We discussed data specifications (e.g., demographic characteristics, PrEP prescriptions, sexually transmitted infections (STI) diagnoses, etc.) with site leaders and adapted the list of requested variables based on availability of elements within the EMR, the type of EMR used, and workflow of each CHC.

**Table 1 pone.0285858.t001:** Electronic medical record (EMR) data collected monthly during the stepped-wedge cluster randomized trial (SW-CRT).

*Primary Outcome*		
**Data Variable**	**Brief Description**	**RE-AIM Dimension**
PrEP uptake	Number of patients initiating PrEP	Effectiveness
*Secondary Outcomes*		
**Data Variable**	**Brief Description**	**RE-AIM Dimension**
Total patients eligible to learn more about PrEP	All patients eligible to learn more about PrEP according to study criteria. All patients 18 years or older, who are not HIV positive who have a medical encounter during which PrEP could be prescribed.	Reach
Demographics/clinical factors of total patients eligible to learn more about PrEP	Demographic data for patients eligible to learn more about PrEP.^a^	Reach
HIV risk assessment	Proportion of patients who undergo HIV risk assessment at each site	Reach
Demographics/clinical factors of patients receiving HIV risk assessment	Demographic data for patients who undergo HIV risk assessment.^a^	Reach
PrEP eligibility	Proportion of patients identified as PrEP eligible at each site.	Reach
Demographics/clinical factors of PrEP eligible patients	Demographic data for patients identified as PrEP eligible.^a^	Reach
Number of providers who educate patients about PrEP	Number of providers who offer PrEP education	Reach
Number of providers who prescribe PrEP	Number of providers who prescribe PrEP to participants	Reach
PrEP education	Proportion of patients who received PrEP education.	Reach
Demographics/clinical factors of PrEP educated patients	Demographic of patients who received PrEP education.^a^	Reach
PrEP offered	Proportion of patients offered PrEP.	Reach
Demographics/clinical factors of patients offered PrEP	Demographics of patients offered PrEP.^a^	Reach
PrEP navigation	Number of patients receiving PrEP navigation services	Reach
Demographics/clinical factors of PrEP navigated patients	Demographics of patients receiving PrEP navigation services.^a^	Reach
Demographics/clinical factors of patients who uptake PrEP	Demographics of patients initiating PrEP.^a^	Effectiveness
Number of providers receiving feedback	Number of CHC providers receiving feedback regarding their PrEP prescription rates	Effectiveness
PrEP ineligibility	Proportion of patients previously identified as PrEP eligible who are ineligible medically to start PrEP.	Effectiveness
Demographics/clinical factors of PrEP ineligible patients	Proportion of patients identified as PrEP ineligible.^a^	Effectiveness
PrEP persistence: Total time on PrEP	Proportion of patients who achieve 6-month persistence on PrEP. Total time on PrEP is measured from date of first prescription to end of last prescription.	Maintenance
Demographics/clinical factors of patients who meet the PrEP persistence Total time on PrEP measure	Demographics of patients who achieve 6-month persistence on PrEP.^a^	Maintenance
PrEP persistence: Proportion of days covered	Proportion of patients who achieve 6-month persistence on PrEP at each site. Patients are considered persistent if they have received a PrEP prescription to cover 6/7 days for each week within a given time period.	Maintenance
Demographics/clinical factors of patients who meet the PrEP persistence: Proportion of days covered measure	Demographics of patients who achieve PrEP persistence via the proportion of days covered measure.^a^	Maintenance

PrEP: Pre-exposure Prophylaxis; STI: Sexually Transmitted Infection; CHC: Community Health Clinic

^a^stratified by race, sex, ethnicity, age group, current gender, sexual identity, current medical complaint, and STI testing history in last year

We will collect both patient-level and clinic-level data from each CHC on a monthly basis. These data will be collected in two ways: 1) by the aggregation of data from patient-level EMR records and 2) by surveys among patients and providers designed to measure knowledge, beliefs, and satisfaction regarding PrEP and the implementation strategies. All EMR data will be collected during each of the three phases of the stepped-wedge trial: 1) pre-implementation; 2) transition, and 3) implementation phases. Table 1 shows the list of EMR variables that will be collected from each site on a monthly basis during the stepped-wedge trial. To obtain these EMR variables, we will aggregate data from individual patient records (~3,000) that meet each variable definition. No recruitment of patients is required for the monthly EMR data collection, as POWER Up is considered part of routine care. The survey data that will be collected vary in the stages of the stepped-wedge trial and the frequency of assessment. Some of these measures will be collected and evaluated monthly, and some will be collected once for pre- and post-implementation (i.e., pre-implementation and at the end of the implementation period). Clinical champions at each site will assist with monitoring adherence to implementation protocols at each site. Table 2 shows outcomes that will be collected via quantitative surveys and qualitative interviews based on the RE-AIM framework [37] and their associated time periods of collection. These surveys and interview guides will be composed of previously validated questions whenever possible and include CFIR domains to assess implementation success. CHC providers and patients will be recruited to complete these quantitative surveys and qualitative interviews via the same recruitment methods used for pre-implementation focus groups (e.g., provider recruitment emails and routine phone calls/recruitment flyers for patients).

**Table 2 pone.0285858.t002:** Data collected for evaluation of implementation using the RE-AIM framework.

Data Variable	Time Collected from Healthcare Network	Brief Description & Source of Data	RE-AIM Dimension
Change in provider knowledge and attitudes about PrEP	Once during control period (baseline) and once at end of implementation period	Average change in score between baseline and post implementation survey about provider knowledge and attitudes about PrEP; qualitative interview	Effectiveness
Change in patient knowledge and attitudes about PrEP	Once during control period (baseline) and once at end of implementation period	Average change in score between baseline and post implementation survey about patient knowledge and attitudes about PrEP; qualitative interview	Effectiveness
Number of providers who complete training	Once after provider training	Number of providers who complete online training	Adoption
Acceptability for providers	Once at end of implementation	Average score among providers of the Acceptability of Intervention Measure tool (AIM); qualitative interviews	Implementation
Acceptability for patients	Once at end of implementation	Average score among patients of the Acceptability of Intervention Measure tool (AIM); qualitative interviews	Implementation
Appropriateness of implementation for providers	Once at end of implementation	Average score among providers of the Intervention Appropriateness Measure tool (IAM); qualitative interviews	Implementation
Appropriateness of implementation for patients	Once at end of implementation	Average score among patients Intervention Appropriateness Measure tool (IAM); qualitative interviews	Implementation
Maintenance of implementation for providers	Once at end of implementation	Average score among providers of the Program Sustainability Assessment Tool (PSAT); qualitative interviews	Maintenance
Feasibility of implementation for providers	Once at end of implementation	Average score among providers on the Feasibility of Intervention Measure tool (FIM); qualitative interviews	Implementation

RE-AIM: Reach, Effectiveness, Adoption, Implementation, Maintenance; PrEP: Pre-exposure Prophylaxis; AIM: Acceptability of Intervention Measure; IAM: Intervention Appropriate Measure; PSAT: Program Sustainability Assessment Tool; FIM: Feasibility of Intervention Measure

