## Trial status

The pre-implementation phase will end in June 2023 (i.e., the stepped-wedge trial is currently in the six-month control period). For the first three sites, the transition period of the implementation phase will begin in July 2023, with these three randomized CHCs receiving training and information on the bundle of POWER Up implementation strategies. These same three sites will begin their implementation period in January of 2024.The research team will modify procedures as needed to ensure successful implementation at each CHC.

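### The stated EMR collection window (July 2023 to December 2025) conflicts with the trial's own schedule and, if it means dates of service, leaves the three wave 1 clinics without control data

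*Protocol article*

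**What the plan says.** Under Data collection: Implementation phase, the article introduces Table 1, whose first row is the primary outcome, PrEP uptake. It dates the table's variables: "These variables will be collected from July 1, 2023 to December 31, 2025".

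Five other places bear on that date:

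- Data collection: Pre-implementation phase: "The pre-implementation phase will occur from September 2021 to June 2023".
- Trial status says that before July 2023 "the stepped-wedge trial is currently in the six-month control period", and then: "For the first three sites, the transition period of the implementation phase will begin in July 2023". The same three sites start implementation in January 2024.
- Study design justifies the stepped wedge on the ground that "each clinic provides data under both the control and implementation conditions".
- Data collection: Implementation phase, in the text after Table 1: "All EMR data will be collected during each of the three phases of the stepped-wedge trial: 1) pre-implementation; 2) transition, and 3) implementation phases".
- The Discussion refers to three years of implementation and evaluation.

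Aims and objectives adds that PrEP prescription rates before and after implementation are to be compared at each CHC.

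**The concern.** The window opens in the month in which wave 1 leaves control. The only control time those three clinics have falls before it. Taken at face value, the date means that the primary outcome is never observed under usual care in a quarter of the clusters, and that the single step with every clinic in control is not captured.

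The practical risk is concrete. Extracts are prepared by an honest broker at each CHC from a stated list of variables and dates. A broker who follows the stated dates would leave out the baseline step. Without it, the comparison before and after implementation at each CHC, and the within-clinic plots of control against implementation rates described under Quantitative data, could not be produced for wave 1.

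**Working it through.** **Inputs from the article.** 12 clinics; 4 waves of 3; six-month steps; one six-month transition per clinic (Study design). Wave 1 is in transition from July 2023 and in implementation from January 2024; a six-month control period precedes this (Trial status). The EMR window is July 1, 2023 to December 31, 2025.

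**Inferred.** The control period is January–June 2023, being six months ending in June 2023. Waves 2–4 follow at six-month intervals. Fig 2, the timeline, is not available here, so these later dates rest on the step length.

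**Length of the window.** July–December 2023 is 6 months; 2024 and 2025 add 24. Total 30 months, and 30 / 6 = 5 steps. Adding January–June 2023 gives 36 months, or 36 / 6 = 6 steps, which is the length that fits the three-year period in the Discussion.

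**Layout** (C control, T transition, I implementation; 3 clinics per row):

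| Wave | Jan–Jun 23 | Jul–Dec 23 | Jan–Jun 24 | Jul–Dec 24 | Jan–Jun 25 | Jul–Dec 25 |
|---|---|---|---|---|---|---|
| 1 | C | T | I | I | I | I |
| 2 | C | C | T | I | I | I |
| 3 | C | C | C | T | I | I |
| 4 | C | C | C | C | T | I |

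**Clinic-periods.**

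- All six steps: control 3 × (1 + 2 + 3 + 4) = 30; transition 3 × 4 = 12; implementation 3 × (4 + 3 + 2 + 1) = 30. Total 72.
- Stated window (first column removed): control 3 × (0 + 1 + 2 + 3) = 18; transition 12; implementation 30. Total 60.
- Control clinic-periods lost: 30 − 18 = 12, and 12 / 30 = 40%. These 12 are the one step with all clinics in control.
- Clinics with no control data: wave 1, 3 / 12 = 25%.

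**Effect on precision.** The article gives no intra-cluster correlation (ICC) or clinic size, so ranges are assumed. The model has fixed period effects, a random clinic effect and a random clinic-by-period effect, with transition cells excluded. With total variance 1 and cluster autocorrelation r, the variance of a clinic-period mean of m women is ICC·r + ICC·(1 − r) + (1 − ICC)/m. The covariance between two periods in the same clinic is ICC·r. The variance of the effect is the matching diagonal element of the inverse of the sum over clinics of X′V⁻¹X. Ratio of that variance, stated window to all six steps, at r = 1 (r = 0.8 in brackets):

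| m | ICC 0.001 | ICC 0.01 | ICC 0.05 | ICC 0.10 |
|---|---|---|---|---|
| 40 | 1.00 (1.00) | 1.05 (1.04) | 1.13 (1.11) | 1.15 (1.13) |
| 250 | 1.03 (1.02) | 1.14 (1.11) | 1.17 (1.14) | 1.17 (1.15) |
| 1,500 | 1.12 (1.09) | 1.17 (1.14) | 1.18 (1.15) | 1.18 (1.15) |

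The variance therefore rises by about 0–18% and the standard error by about 0–9% (√1.18 ≈ 1.09). The effect is estimable throughout.

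**The case against.** The strongest reply is that control data were plainly intended. Study design says every clinic supplies them, the text after Table 1 includes the pre-implementation phase, and Quantitative data analyses control-period observations. One date stands against several statements. Nor does the article say that the dates are dates of service: with monthly collection, they could describe when transfers run. Routine records can be extracted later, and the precision cost is small even in the worst case computed. This stands in so far as the loss is conditional and not established. It does not remove the contradiction, because the article never says which statement governs, and the date is attached to the primary outcome.

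Three stronger readings are tempting, and the documents do not support them.

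- *Women already on PrEP would be counted as new starters, biasing the effect toward the null.* Nothing says that initiation is judged only from prescriptions inside the window, and how it is coded can properly sit in the full protocol or analysis plan. With period effects and transition excluded, every analysed July–December 2023 cell is control, so an inflation common to that period is absorbed by its period effect: adding a constant to those cells moves the estimate by zero to rounding error. No look-back rule is therefore called for on this ground.
- *Wave 1 would inform the effect only through comparison between clinics.* Not so. Its implementation periods help to identify the time trend for the later waves. With the clinic variance made very large, so that only within-clinic information counts, removing wave 1 from the stated window about doubles the variance (ratio 2.04). What wave 1 would lack is its own contrast of control with implementation.
- *The window opens on the very day wave 1 leaves control.* Trial status gives the month only.

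**Conclusion.** The stated window is wrong or incomplete as written. It contradicts the control-period dates under Trial status and Data collection: Pre-implementation phase, the design premise under Study design, the three-phase EMR coverage stated after Table 1, and the three-year period in the Discussion.

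What is at stake, should the window govern dates of service, is the missing control data and pre/post comparison for a quarter of the clinics and the missing all-control step. Power is a minor issue. These counts rest on the inferred January–June 2023 control step and the inferred dates for waves 2–4; that wave 1 has no control time inside the window follows from the stated dates alone. The precision figures rest on the assumed ranges of ICC 0.001–0.10, cluster autocorrelation 0.8–1.0 and 40–1,500 women per clinic-period. A reader should not conclude that the baseline has in fact been lost.

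**What to change.** State that EMR dates of service start with the six-month control period (January 2023, inferred from Trial status) at all 12 clinics, and pull those records retrospectively. Align the window under Data collection: Implementation phase with Study design, Data collection: Pre-implementation phase, the phase coverage stated after Table 1, and Trial status. If July 1, 2023 is only the date on which transfers begin, say so and give the dates of service separately.

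The cost is a wording change, one retrospective extraction in each of the three networks, and possibly a date edit to the data use agreements, whose terms are not shown. The EMR data need no patient recruitment.
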